# Effects of moderate-intensity intermittent hypoxic training on health outcomes of patients recovered from COVID-19: the AEROBICOVID study protocol for a randomized controlled trial

**DOI:** 10.1186/s13063-021-05414-2

**Published:** 2021-08-12

**Keywords:** Exercise, Hypoxia-inducible factor 1 alpha subunit, Inflammation, Respiratory function tests, SARS virus

## Abstract

**Background:**

Recent studies point to a lower number and reduced severity of cases in higher altitude cities with decreased oxygen concentration. Specific literature has shown several benefits of physical training, so, in this sense, physical training with hypoxic stimulus appears as an alternative that supports the conventional treatments of the COVID-19 patient’s recovery. Thus, this study’s primary aim is to analyze the effects of moderate-intensity intermittent hypoxic training on health outcomes in COVID-19 recovered patients.

**Methods:**

A clinical trial controlled double-blind study was designed. Participants (30–69 years old) will be recruited among those with moderate to severe COVID-19 symptoms, approximately 30 days after recovery. They will be included in groups according to the training (T) and recovery (R) association with hypoxia (H) or normoxia (N): (a) T_H_:R_H_, (b) T_N_:R_H_, (c) T_N_:R_N_, and last (d) the control group. The 8-week exercise bike intervention will be carried out with a gradual load increase according to the established periods, three times a week in sets of 5 min, 90 to 100% of the anaerobic threshold (AT), and a 2.5-min break. Blood will be collected for genotyping. First, after 4 weeks (partial), after 8 weeks, and later, 4 weeks after the end of the physical training intervention, participants will perform assessments. The primary outcome is the maximum oxygen consumption (VO_2_peak). The secondary outcomes include lung function, inflammatory mediators, hematological, autonomic parameters, AT, body composition analysis, quality of life, mental health, anthropometric measurements, and physical fitness. The statistical analysis will be executed using the linear regression model with mixed effects at a 5% significance level.

**Discussion:**

This study is designed to provide evidence to support the clinical benefits of moderate-intensity intermittent hypoxic training as a part of the treatment of patients recovered from COVID-19. It may also provide evidence on the efficacy and safety of intermittent hypoxic training in different health conditions. Lastly, this study presents an innovative strategy enabling up to 16 participants in the same training session.

**Trial registration:**

ClinicalTrials.gov RBR-5d7hkv. Registered after the start of inclusion on 3 November 2020 with the Brazilian Clinical Trials Registry

**Supplementary Information:**

The online version contains supplementary material available at 10.1186/s13063-021-05414-2.

## Background

In March 2020, the World Health Organization raised the state of COVID-19 contamination to the pandemic. Currently, infections have exceeded 175 million cases and 3.8 million deaths. News related to COVID-19 is commented on daily in the media and has caused great concern and impact on Global Public Health [1].

Symptoms presented by those infected with COVID-19 are common to other respiratory infections. They may include fever, cough, sore throat, headache, fatigue, muscle pain, loss of smell, and shortness of breath. The clinical condition is diverse, ranging from an asymptomatic state to acute respiratory syndrome and damage to various body systems, increasing inflammatory markers, cardiovascular alterations, and injuries to the lungs and kidneys. The worldwide mortality rate of COVID-19 ranges from 2 to 3%, so most people recover from the disease. However, it is important to highlight that a significant part of this recovered population presents persistent symptoms or sequelae after the recovery; thus, they could be investigated [2–4].

Recent studies indicate that people who live at altitude with low levels of oxygen (O_2_) have a lower prevalence of COVID-19 and less severity in cases of infection [5–10]. The factors that may be related to lower susceptibility to COVID-19 involve physiological and anatomical adaptations in the lungs, with perfusion and capacity improvements, but mainly hypoxia-inducible-factor-1α (HIF-1α) activation [5–7], which has become scientifically relevant due to its discovery behind the Nobel Prize in Physiology or Medicine in 2019 [11]. Furthermore, according to the phenomenon of hormesis, moderate doses of intermittent hypoxia would lead to the activation of HIF-1α, triggering positive adaptations in the face of different diseases [12].

Specifically concerning COVID-19, HIF-1α can decrease the expression of the angiotensin-converting enzyme (ACE)2, which is indicated as a facilitator of the SARS-CoV2 virus into cells, mainly in the lungs [6, 7, 13]. HIF-1α production increases the expression of ACE1, stimulating the formation of angiotensin II, which regulates angiotensin II type 1 receptor (AGTR1). This process would reduce the expression of ACE2 [5, 6]. The infection with SARS-CoV2 leads to the destruction of epithelial cells, representing an important part of airway immunity. Consequently, a series of changes in immunological and inflammatory markers is triggered [14, 15]. Still, it is important to note that HIF-1α can increase the gene expression to produce erythropoietin (EPO), countering the harmful effects of covid-19. Among EPO’s benefits are highlighted: neuroprotection, central ventilation stimulation, endothelium protection, and pulmonary vasodilation, red blood cell production, and anti-inflammatory effect [16].

On the other hand, moderate-intensity interval exercise can reduce chronic inflammation and strengthen the immune system [17–20], reducing the severity and mortality of viral diseases [21]. In addition, higher aerobic capacity can produce short-term improvements in the immune and respiratory systems [22], both affected by COVID-19 [23].

Training methods using hypoxia as a resource have existed since the 1960s to increase performance at sea level or generate acclimatization for athletes to improve their performance in altitude tests [24, 25]. More recent studies [25–30] have shown that this type of intervention can provide good health outcomes and that physical training under normobaric hypoxia is safe and can be performed with different populations. For example, studies developed with overweight and obese women showed that a reduction of fat mass has been reported with a concomitant increase in lean mass [26] and cardiorespiratory fitness [27]. These results were better in the groups that performed interval training or sprints in hypoxia than those trained in normoxia after 12 weeks (36 sessions). Also, it has been reported the effects on bone mineral density in older adults, but only the group that underwent training of whole-body vibration in hypoxia showed improvements after 18 weeks (36 sessions), while the group that trained in normoxia did not improve [28]. Additionally, in another study performed over 3 weeks (9 sessions), the aerobic capacity, HIF-1α, nitric oxide, and pro-angiogenic factors improved, but only in the group of active young men who performed high-intensity interval training under hypoxic conditions on a bicycle [29]. Moreover, a systematic review and meta-analysis identified that hypoxic training promoted better responses in reducing triglycerides and increasing muscle mass than the same exercise performed in normoxia [30].

Although the studies previously mentioned [26–29] had shown health benefits for participants right after the intervention, a recent study [31] that performed high-intensity training under hypoxic conditions found effects after 4 weeks of the end of the intervention. At that moment, the trunk fat mass of overweight and obese women decreased significantly compared to the intervention’s result. This result may indicate that the adaptations promoted by the hypoxic training can last longer since this improvement after 4 weeks from the end was not found in the group that trained in normoxia.

Even though exposure to physical training and hypoxia can result in several health benefits, the response magnitude can vary considerably between individuals. Genetic characteristics could explain this variation and the different reactions that patients recovered from COVID-19 present in the gradual recovery process. The COVID-19 number and severity of cases in some populations have been associated with ACE gene and the frequency of I allele (insertion) or D allele (deletion) of 287-bp, drawing attention to the activity of this protein, which has a relationship with these genetic variants [32]. However, the results are still preliminary and point to this relationship’s complexity, requiring further exploration. Furthermore, since the modulation of ACE2 by HIF-1α involves the regulation of AGTR1, the investigation of genetic variants related to this receptor may also be necessary to understand this context better [9, 10]. Genetic variation could also influence the response to training in hypoxia, and these analyses may explain why some people present more physical training benefits than others. For example, the DD genotype of ACE may be related to a worse adaptation in altitude, and the presence of the I allele may indicate a better possibility of adaptation [33]. There is also evidence about an association between EPO’s production and genetic variants of the promoter region of this gene [34].

Thus, we hypothesize that training in normoxia would promote improvements in health status comparing to the control group that will not train. Both groups that will train in hypoxia would present even better results than the normoxia group, helping in the faster and more complete recovery of the organism, restoring immune system homeostasis and cardiorespiratory capacity. Still, it is expected that the studied genetic variants would affect the magnitude of response to the intervention.

## Methods

This protocol was written in accordance with the Standard Protocol Items: Recommendations for Interventional Trials guidelines (SPIRIT) [35]. We used the SPIRIT checklist when writing our report [36].

### Aims

#### Primary aim

To analyze the effects of moderate-intensity intermittent hypoxic training on the health outcomes of patients recovered from COVID-19.

#### Secondary aims

To describe the health status post-COVID, patients recovered who had presented moderate to severe symptoms will be assessed through lung function (spirometry), hematological and serum biochemical (complete blood cell count, including hemoglobin, red blood cell, white blood cell, lymphocyte, neutrophil, and platelet; glucose; triglycerides, total cholesterol, and fractions; lactate dehydrogenase; liver enzymes, such as alanine aminotransferase and aspartate aminotransferase; and EPO), immunological (cytokines, such as IL-6, IL-8, IL-10, and TNF-α; and, lipid mediators, such as eicosanoids), and autonomic parameters (heart rate variability), in addition to physical fitness (motor tests), quality of life (SF – 12), and mental health (DASS – 21).

To analyze the effects of moderate-intensity intermittent hypoxic training in patients recovered from COVID-19 who presented moderate to severe symptoms on:
Hematological parameters, using the complete blood cell count and other biochemical analyses; immunological ones through inflammation markers (cytokines and lipid mediators); and erythropoiesis through EPO analysisPhysical fitness through aerobic power, aerobic capacity, strength resistance of lower limbs, agility, and dynamic balanceAnthropometric measurements and body composition through the distribution of lean, bone, and adipose tissueBlood pressure and autonomic parameters through heart rate variability (HRV)Quality of life through 12-item Short-Form Health Survey (SF-12), and the state of mental health through the assessment of levels of depression, anxiety, and stress, using the Depression, Anxiety and Stress Scale (DASS - 21)

To determine the effects after 4 weeks of the end of the moderate-intensity intermittent hypoxic training on lung function, hematological, immunological, and autonomic parameters and physical fitness, quality of life, and mental health in COVID-19 recovered patients with previous moderate to severe symptoms.

To analyze the influence of genetic variants of ACE, AGTR1, a promoter region of the EPO gene, and the EPO receptor on the effects of moderate-intensity intermittent hypoxic training in COVID-19 recovered patients.

### Design and setting

The study design is based on a randomized, double-blind controlled clinical trial composed of four groups. The control group being formed by the participants who are not available to participate in the intervention and accept to carry out a follow-up through the evaluations; and the physical training groups randomly divided according to the association of training (T) and recovery (R) with hypoxia (H) or normoxia (N): (a) T_H_:R_H_, (b) T_N_:R_H_, and (c) T_N_:R_N_. The allocation ratio will be 1:1:1:1.

As Fig. 1 shows, the experimental protocol will consist of (i) familiarization and carrying out the initial assessments (evaluation 1) in the three sessions of week 0; (ii) 8-week intervention with a partial assessment to adjust the training load on week 5 (half of the intervention – evaluation, (2) (iii) reassessments on week 9, following the end of physical training intervention (evaluation 3), and (iv) reassessments on week 13, four after the end of the intervention (evaluation 4).

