### Recruitment

The invitation will be made to the Health Institutions to offer the possibility of participating in this research to patients who have had moderate to severe symptoms approximately 30 days after the recovery of clinical signs or medical discharge (hospitalized people). Furthermore, the disclosure will happen for the entire population of Ribeirão Preto, SP, Brazil, and the region through the local television channels, USP’s local radio and news from the internet, social networks, and among other media outlets. Participants will be asked to complete the evaluations on week 0. After that, they will be assigned randomly to each group. This study will develop every effort to control confounding variables. Randomization and allocation will be performed by the research coordinator. Considering special randomization techniques, in this project, we will be using the randomization of matched pairs [42], considering a baseline pairing strategy regarding confounding variables such as sex, age, and level of physical conditioning of the participants for their selection and random assignment in the research groups. As there are three training groups, (a) T_H_:R_H_, (b) T_N_:R_H_, and (c) T_N_:R_N_, pairing groups will be organized consisting of participants based on the matching characteristics above, which will be drawn randomly using Microsoft Excel for allocation to groups. This method is satisfactory and suitable for intervention studies in which there are not many participants. In terms of blinding, only the research coordinator is aware of the allocation. Different researchers will work on the intervention and collect information from the participants as evaluations, who will be blinded to avoid potential bias. To maintain the overall quality and legitimacy of the clinical trial, unblinding should occur only in exceptional circumstances when knowledge of the actual treatment is essential for further management of the patient.

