## Discussion

It is plausible that the convalescent people of COVID-19 who showed moderate to severe symptoms are in the process of gradual recovery and still have changes in their health status, even after approximately 30 days of recovery from clinical signs or medical discharge. Therefore, the monitoring control group that will not train will describe the effects of COVID-19 on lung function, hematological, immunological, autonomic parameters, physical fitness, and mental health.

The gradual recovery process of the participants will be observed according to the association of training (T) and recovery (R) with hypoxia (H) or normoxia (N). Therefore, it is expected that the normoxia training and recovery group (T_N_:R_N_) can show better results compared to the control group. Besides, both groups that will train in hypoxia may demonstrate even better results than the T_N_:R_N_ group, with a higher result for the group that will perform the training in normoxia and the recovery in hypoxia (T_N_:R_H_), comparing the group that will perform training and recovery in hypoxia (T_H_:R_H_). The justification for these two groups to train differently associated with hypoxia is that exercise intensity can be reduced with hypoxia exposure. In this way, to minimize this possibility, the group that will breathe hypoxia air only during the pause could perform the training stimulus in greater intensity (normoxia).

The expectation is that physical activity can be used to face the COVID-19 pandemic and other health problems as a complementary treatment. The consolidated evidence on the benefits of physical activity for physical, physiological, social, and mental health and the knowledge generated by this research project may contribute to solving priority health problems in Brazil. Furthermore, this project’s results may contribute to the qualification of health care practices and promote scientific, technological, and innovation development in the Health area, aiming at strengthening the Unified Health System of Brazil.

Still, it is expected that the genetic variants studied may be associated with the recovery process of the convalescents of COVID-19 and with the effect of moderate training combined with intermittent normobaric hypoxia. The study of genetic variants can bring important advances in understanding the variation in responses related to the triggering and progression of some diseases and the effect of physical training.

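### The study is labelled a four-group 1:1:1:1 randomised trial, but the control group is not randomised, so training versus control is a non-randomised comparison

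*Protocol article*

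**What the plan says.** Under Design and setting, the protocol article states: "The study design is based on a randomized, double-blind controlled clinical trial composed of four groups". It then says how the groups are filled. On the untrained group: "The control group being formed by the participants who are not available to participate in the intervention"; these people agree to be followed through the evaluations. On the others: "the physical training groups randomly divided according to the association of training (T) and recovery (R) with hypoxia (H) or normoxia (N"). The paragraph ends: "The allocation ratio will be 1:1:1:1".

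Under Recruitment, after the week 0 evaluations, participants are described thus: "After that, they will be assigned randomly to each group". The matched draw that follows, on sex, age and physical conditioning, is introduced with "As there are three training groups" and names only TH:RH, TN:RH and TN:RN.

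The control group is also given an inferential role. The Background hypothesises that "training in normoxia would promote improvements in health status comparing to the control group that will not train", and the Discussion repeats this as an expected result for TN:RN. The Sample size section counts the control group as one of four parallel groups. Strengths and limitations lists only difficulty in reaching participants.

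**The concern.** People who cannot attend three sessions a week for eight weeks may differ from those who can in ways that bear on the outcome: return to work, motivation, illness severity, or fitness. Everyone enters about 30 days after recovery, and the Discussion expects them still to be improving. If available and unavailable people improve at different speeds, the difference would look like an effect of training.

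Randomisation would protect against this, and the label says it is in place. The description of how the control group is formed says it is not. A reader who takes the four-group randomised label at face value would give the training-versus-control estimate a causal standing that the design does not support. One of the stated hypotheses depends on that estimate.

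**Working it through.** **Step 1. Set the statements side by side.**

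| Place in the article | Statement | Control group randomised? |
|---|---|---|
| Design and setting, opening | randomised trial of four groups | yes, by label |
| Design and setting, control group | formed from people unavailable for training | no |
| Design and setting, training groups | these are randomly divided | no; only three groups are drawn |
| Design and setting, ratio | 1:1:1:1 | yes, if read as an allocation ratio |
| Recruitment, general sentence | random assignment to each group | yes, if taken alone |
| Recruitment, matched draw | organised for three training groups | no |

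The two operational descriptions (how controls are formed, and what the draw covers) agree with each other and contradict the label. A group that people enter because they are unavailable cannot also be one to which they are randomly allocated.

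**Step 2. Which contrasts are touched.** TH:RH versus TN:RH, TH:RH versus TN:RN and TN:RH versus TN:RN all lie within the random draw and are unaffected. Each training group versus control, and any pooled training group versus control, lies outside it.

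**Step 3. The plan's own figures.** The Sample size section gives 20 per group, 4 × 20 = 80, and 80 × 1.10 = 88, or 22 per group. The 20 cannot be reproduced from the stated inputs (80% power, 5% level, 10% difference) because no SD is given. Solving for the SD, two-sided:

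- Normal approximation: SD = 10 × √(20/2) / (1.960 + 0.842) = 11.3% of the mean.
- t test: 80% power at 20 per group needs a standardised difference of 0.909, so SD = 10/0.909 = 11.0% of the mean.

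**Step 4. Illustration of bias.** Assumptions: SD 11% of the mean, 20 versus 20, two-sided 5% t test, no true training effect, and a selection difference b between trainees and controls. The documents do not give b or the SD.

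Noncentrality = (b/SD) / √(1/20 + 1/20) = (b/11) / 0.3162, with 38 degrees of freedom and critical value 2.024. The false-positive rate is the probability that |t| exceeds 2.024.

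| b, % of mean | Noncentrality | Rate at SD 11% |
|---|---|---|
| 0 | 0 | 5.0% |
| 1 | 0.287 | 5.9% |
| 2 | 0.575 | 8.7% |
| 3 | 0.862 | 13.4% |
| 5 | 1.437 | 28.9% |

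The result depends on the SD. At SD 20% of the mean, b = 5% gives 12.0%. More participants would not help: for a fixed b the noncentrality grows with the sample size.

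**The case against.** The article does not hide how controls are formed, and it says that the training groups are the ones randomly divided. The sentence on random assignment to each group is qualified by what follows it, and 1:1:1:1 can be read as four equal planned sizes of 22. The primary aim concerns hypoxic training, and the Statistical analysis section speaks of comparing types of training (hypoxia and normoxia). All this stands, and it limits the point to the control contrast. It does not remove the contradiction, because the article still calls all four groups randomised and still states a hypothesis against control.

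Several stronger readings are tempting but not supported:

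- A reader might infer that the trial's randomised evidence as a whole is compromised. It is not: the hypoxia-versus-normoxia contrasts are intact.
- A reader might infer that no confounder adjustment will be made, because covariates are named only for binary outcomes. An article commonly leaves covariate lists to the analysis plan, and Recruitment promises efforts to control confounding. Silence here is not evidence.
- A reader might infer that the control contrast will be reported as a randomised effect, or that the model will force equal baselines. No section says either.
- A reader might quote a false-positive rate of 80% for a 10% selection difference. That is circular: a bias equal to the planned effect is detected at the planned power.
- A reader might object to the Discussion's statement that "the monitoring control group that will not train will describe the effects of COVID-19 on lung function", since no uninfected or pre-infection comparator is described. The preceding sentence is about gradual recovery, so the natural-course meaning is clear. This is a minor matter of wording.

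Two further limits apply. The common entry criteria (moderate to severe symptoms, about 30 days since recovery) narrow differences in recovery stage without removing them. Repeated measures from baseline deal with some baseline imbalance, but not with different trajectories.

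**Conclusion.** The design statement is wrong as written. This is a three-arm randomised comparison with a concurrent, self-selected untrained cohort. The comparison of training with control, including the stated TN:RN hypothesis, is non-randomised and open to confounding by factors linked to availability and by different recovery trajectories.

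That conclusion follows from the text and needs no number. The size and direction of any bias are unknown. The rates of about 6% to 29% for selection differences of 1% to 5% of the mean only show how such a bias would act. They rest on an SD back-solved from the sample size, which need not be the SD of change over time, on assumed selection differences, on a two-sided test and on an unadjusted two-group comparison.

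**What to change.** 1. Describe the study as a three-arm 1:1:1 randomised trial (TH:RH, TN:RH, TN:RN) with a concurrent non-randomised untrained cohort, and align Design and setting, Recruitment and the Abstract with this. If four equal group sizes are meant, say so as a target size and not as an allocation ratio.
2. Base randomised claims on the three training arms only.
3. Label training versus control as a non-randomised comparison wherever the hypothesis appears, and adjust it for a small set of baseline data already planned: baseline VO2peak, age, sex, and either IPAQ level or COVID-19 severity from the anamnesis. With about 20 per group the set should stay small. Days since recovery is an entry criterion but is not listed as a recorded variable, so it should not be assumed available.
4. Add the non-randomised control to Strengths and limitations.

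The cost is wording and a few covariates, with no new participants or procedures. The downside is a weaker claim against control, since adjustment reduces but cannot exclude confounding.
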